## Expected results

5

Based on evidence from comparable psychoeducational interventions and Polish normative PRAQ-R2 data, we anticipate that women in the intervention group will demonstrate a clinically meaningful reduction in PrA at 34–37 weeks of gestation compared to the control group. Secondary outcomes are expected to show improved childbirth satisfaction, lower rates of elective caesarean section without medical indication, and better postpartum psychological wellbeing. These expectations will be formally tested in the trial.

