### Hypotheses

1.3

The following hypotheses will be tested:

*H1*: Women in the intervention group will demonstrate significantly lower levels of PrA at 34–37 weeks of gestation compared to women in the control group receiving standard antenatal care.

*H2*: Women in the intervention group will report significantly lower levels of depressive symptoms, higher childbirth satisfaction, and better maternal and neonatal health outcomes compared to women in the control group.

*H3*: Among all randomised participants, elevated PrA at baseline will be associated with a higher likelihood of caesarean section, less favourable attitudes towards breastfeeding, and poorer maternal and neonatal health outcomes, regardless of group allocation. H3 is an exploratory hypothesis examining the association between baseline anxiety and obstetric outcomes across both groups, independent of treatment allocation.

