#### Secondary outcomes

2.6.2

Anxiety and depressive symptoms will be assessed using the PHQ-4 total score (range 0–12) and two subscale scores: PHQ-2 for depressive symptoms (items 1–2; cut-off ≥3) and GAD-2 for anxiety symptoms (items 3–4; cut-off ≥3). The metric is the change from baseline (Time I) to postpartum assessment (Time III, ≥6 weeks postpartum), with mean scores compared between groups.

Childbirth-related PTSD symptoms will be assessed prenatally using the PTSD-8 total score (range 0–24; no universally established cut-off in the original instrument) at baseline (Time I), and postnatally using the PPQ-II total score and subscale scores at Time III. Mean final values will be compared between groups.

Childbirth satisfaction will be measured using the BSS-R total score at Time III, with mean final values compared between groups.

Perceived social support will be assessed using the MSPSS total score (range 12–84) and three subscale scores (Significant Other, Family, Friends; range 4–28 each) at baseline (Time I) and postpartum (Time III), with mean scores compared between groups.

Infant feeding attitudes will be measured using the IIFAS total score at baseline (Time I) and reported descriptively.

Mode of birth and obstetric outcomes will be collected via the Custom Postpartum Questionnaire (Part B) at Time III and reported as frequencies and proportions.

Although all instruments will be administered in full, not all subscales or total scores will be analysed within the scope of this trial; some data will be reserved for secondary research questions and future analyses. Detailed descriptions of all measurement instruments, including psychometric properties of Polish adaptations, are provided in section 2.12 Data Collection Methods. Formal permissions for the use of all Polish adaptations have been obtained from the respective copyright holders prior to the commencement of the study.

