### Statistical analysis plan

2.14

Analyses will be conducted according to randomised group allocation and will primarily follow the intention-to-treat principle, insofar as outcome data are available. The primary endpoint is PrA measured using the PRAQ-R2 at 34–37 weeks’ gestation. The primary analysis will compare post-intervention PRAQ-R2 scores between groups using analysis of covariance (ANCOVA), with treatment group as the main factor and baseline PRAQ-R2 score as a covariate. The primary outcome is assessed at two prenatal time points only: baseline and post-intervention. The postpartum assessment applies exclusively to secondary outcomes.

Secondary outcomes will be analysed using regression models appropriate to outcome type, with logistic regression for binary outcomes and linear regression for continuous outcomes. Secondary analyses will be considered supportive and exploratory; no formal adjustment for multiplicity is planned. Missing data will be described by study arm and time point. The primary analysis assumes data are missing at random (MAR); this assumption will be examined via sensitivity analysis, using a mixed-effects model for repeated measures applied to all available longitudinal data. Multiple imputation is not planned. The possibility of data missing not at random (MNAR) cannot be excluded and is acknowledged as a limitation. Stratification variables included in the randomisation will be entered as covariates in the primary ANCOVA model. A supportive per-protocol analysis will also be conducted among participants with observed primary endpoint data; in the intervention arm, this will additionally require completion of at least four intervention sessions. Two pre-specified sensitivity analyses will be conducted: (1) a linear mixed-effects model including midwife as a random effect, to account for potential clustering by intervention deliverer; and (2) a mixed-effects model for repeated measures applied to all available longitudinal data under a missing-at-random assumption, to assess the robustness of findings in the presence of incomplete data.

The mode of intervention delivery (in-person versus remote) will be recorded. As the trial is not powered for formal moderator analyses, any comparison by delivery mode will be considered exploratory and interpreted cautiously.

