The evaluation of this intervention may additionally contribute to reducing the rate of medically unjustified caesarean sections by addressing one of their key psychological determinants. Should the trial demonstrate effectiveness, the implications would be two-fold. First of all, it would provide an evidence-based, practical tool for addressing the rising caesarean section rates in Poland—a public health crisis. By reducing the anxiety-driven demand for elective surgical procedures, the intervention could contribute to lowering procedural rates to WHO-recommended levels, thereby reducing associated maternal and neonatal morbidity. Secondly, it would validate a care model that strengthens the role of midwives as autonomous providers of psychological support, potentially informing health policy changes towards more holistic and continuous midwifery-led care models in Poland.

The transferability of findings to other healthcare contexts should, however, be considered carefully. The present intervention is embedded within a specific Polish perinatal care context, characterised by high medicalisation, limited midwifery autonomy, and fragmented continuity of care. Countries with similar structural characteristics—including high caesarean section rates driven by non-medical factors, restricted access to midwife-led care, and comparable cultural attitudes towards childbirth—may represent the most appropriate settings for replication. By contrast, healthcare systems with well-established midwifery continuity models, routine psychosocial screening, or lower baseline anxiety levels may yield different effect sizes. Additionally, cultural norms surrounding mental health, help-seeking behaviour, and the perceived role of midwives in psychological support vary considerably across countries and should be accounted for when adapting this intervention to new contexts.

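### Secondary outcomes are hypotheses to be formally tested in sections 1.3 and 5 but exploratory in 2.14, and 2.6.2 and 2.14 disagree on how mode of birth is analysed

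*Protocol article*

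**What the plan says.** Section 1.3 (Hypotheses) introduces H1, H2 and H3 with "The following hypotheses will be tested". H2 reads "Women in the intervention group will report significantly lower levels of depressive symptoms, higher childbirth satisfaction, and better maternal and neonatal health outcomes", compared with control. Of the three, only the last carries a qualifier: "H3 is an exploratory hypothesis examining the association between baseline anxiety and obstetric outcomes across both groups".

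Section 5 (Expected results) first states the expectation for the primary outcome, then adds "Secondary outcomes are expected to show improved childbirth satisfaction, lower rates of elective caesarean section without medical indication, and better postpartum psychological wellbeing". It closes with "These expectations will be formally tested in the trial".

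Section 2.14 (Statistical analysis plan) states "Secondary analyses will be considered supportive and exploratory; no formal adjustment for multiplicity is planned". It assigns logistic regression to binary secondary outcomes and linear regression to continuous ones.

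Section 2.6.2 (Secondary outcomes) says that mode of birth and obstetric outcomes "will be collected via the Custom Postpartum Questionnaire (Part B) at Time III and reported as frequencies and proportions". Section 1.2 (Objectives) nevertheless makes mode of birth and the rate of elective caesarean without medical indication part of a specific objective.

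The two-sided 5% level appears in section 2.9, for the primary comparison only.

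**The concern.** A reader of sections 1.3 and 5 would take H2 to stand beside H1 as a claim that the trial will confirm or reject. A reader of 2.14 would take the same outcomes as supportive. No section says that H2 is exploratory, and none says what result would count as support for it (one component, or all of them).

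A depression or satisfaction result at p = 0.03 could therefore be reported after the event either as a confirmed hypothesis or as hypothesis-generating, with text in the article to back each version.

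The second inconsistency concerns the analysis itself. Whether caesarean is described by arm or compared between arms depends on whether 2.6.2, 2.14 or 5 is read. This is the secondary outcome on which the article's policy argument rests.

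**Working it through.** **1. Status of the secondary outcomes, section by section**

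| Place | Status given |
|---|---|
| 1.3, lead-in | H1 to H3 are all to be tested |
| 1.3, H2 | Worded as a significant difference; no exploratory label |
| 1.3, H3 | Explicitly exploratory |
| 5 | Secondary expectations listed, then formal testing promised |
| 2.14 | Supportive and exploratory; no multiplicity adjustment |

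The label on H3 alone invites the inference that H2 is not exploratory. Section 2.14 says the opposite for every secondary analysis. Both cannot govern how H2 is reported.

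**2. Mode of birth and caesarean, section by section**

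| Place | Analysis given |
|---|---|
| 2.6.2 | Frequencies and proportions |
| 2.14 | Logistic regression for binary outcomes |
| 5 | Formal test of lower elective caesarean rates |

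These are three different treatments: descriptive, modelled, and formally tested.

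**3. Illustration of what the status decides**

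The article states no error rate for the secondary outcomes, so there is no figure of its own to reproduce. The inputs are:

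- k = 4, the domains named in H2: depressive symptoms, childbirth satisfaction, maternal outcomes and neonatal outcomes.
- Two-sided 5% per test. This is an assumption, because 2.9 gives alpha only for the primary.
- One test per domain, no true effects, and any one success counted as support for H2. These are also assumptions, as no success rule is given.

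For independent tests, the chance of at least one false positive is 1 − (1 − 0.05)^4 = 1 − 0.8145 = 0.185.

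For correlated tests, take normal test statistics with a common correlation ρ and reject when |z| > 1.96. The chance is 1 − P(all four |z| ≤ 1.96):

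| ρ | Chance of at least one false positive |
|---|---|
| 0 | 18.5% |
| 0.3 | 17.4% |
| 0.5 | 15.6% |
| 0.8 | 11.4% |

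The range is about 11% to 19%, against a nominal 5%. If all four components had to succeed, the chance would be below 5%. The missing success rule therefore matters as much as the number of tests.

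**The case against.** The strongest reply is that section 2.14 is the operative text. The article says that its statistical analysis plan is published within it, and 2.14 calls all secondary analyses exploratory. Section 2.9 adds that the study is meant to give an initial estimate for a larger trial, and section 5 is a short narrative that sets no analysis rule. An analyst who follows 2.14 cannot report H2 as confirmed. This stands, and it contains most of the harm.

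It can also be said that being tested does not mean being confirmatory, since H3 sits under the same lead-in and is exploratory. The closing sentence of section 5 covers the primary expectation too, and in H2 the word for significance directly precedes only the depression component. These points soften the contradiction without removing it: H2 still lacks the label that H3 has, and the promise in section 5 follows directly on a list of secondary outcomes.

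Three stronger readings are tempting, and the documents do not support them.

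- A reader might infer that the missing multiplicity adjustment is itself a defect. For outcomes declared exploratory it is not.
- A reader might infer that under 2.14 caesarean is never compared between arms. In fact 2.14 provides logistic regression for binary outcomes, so the conflict is between 2.6.2 and 2.14.
- A reader might count every score compared in 2.6.2 and reach a much larger error rate for H2. That count would include the social-support scores and the GAD-2 anxiety score, which are not in H2, and 2.6.2 says that not all scores will be analysed.

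**Conclusion.** The point holds as an inconsistency of status, with a smaller inconsistency in how mode of birth is analysed. It is a reporting risk. The primary analysis, its alpha and the sample size are not touched.

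The size is illustrative: an 11% to 19% chance of at least one false claim under H2. It rests on four tests, an assumed two-sided 5% for each, no true effects, and a rule that any one success suffices. If 2.14 is followed to the letter in the report, the risk is largely contained.

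A reader might go further and infer from section 4 (Discussion) that a positive anxiety result is to be taken as proof of an effect on caesarean rates, since it says of a successful trial that "it would provide an evidence-based, practical tool for addressing the rising caesarean section rates in Poland". That passage is discussion, is partly hedged and sets no decision rule, so it does not carry a finding of its own. Nor can the precision for elective caesarean without indication be calculated from the article. The national rate of 48.4% in section 1.1.4 covers all caesareans, and women with absolute or strong medical indications are excluded from the trial.

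**What to change.** - **1.3:** keep H1, on the PRAQ-R2 total score at 34–37 weeks, as the only confirmatory hypothesis. Label H2 exploratory, as H3 already is, and remove the word for significance from it.
- **5:** replace the closing sentence with one saying that only the primary expectation is formally tested, and that secondary outcomes are estimated with 95% confidence intervals and interpreted as exploratory.
- **2.6.2:** align with 2.14 by reporting mode of birth and elective caesarean as a between-arm comparison with a 95% confidence interval, alongside the frequencies.
- **4 (optional):** add that a positive primary result shows an effect on pregnancy-related anxiety only.

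The cost is wording. No data, participants or procedures are added. The one loss is that H2 can no longer be reported as a confirmed hypothesis. The change should be made before outcome data are seen, so that the status is not chosen afterwards.

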## Conclusion

6

This RCT protocol presents a novel and contextually adapted approach to addressing the intertwined challenges of high PrA in Poland. By testing a midwife-delivered psychoeducational programme, the study addresses a clear clinical need while contributing to the broader scientific understanding of non-pharmacological interventions in perinatal mental health. If proven effective, this intervention has the potential to improve the psychological wellbeing of pregnant women, promote physiological childbirth and inform the evolution of more supportive and empowering perinatal care practices in Poland as well as in similar healthcare settings.

### Oversight

The study is overseen by the research team at the Division of Obstetric and Gynaecological Nursing, Medical University of Gdańsk. No independent steering committee or data monitoring committee has been established, given the small sample size and low-risk nature of the psychoeducational intervention. Trial monitoring will be conducted by the principal investigator in accordance with the procedures described in the Trial Monitoring section.

### Protocol and statistical analysis plan

The full trial protocol and statistical analysis plan are published as part of this manuscript. Any supplementary analytical details are available upon request from the corresponding author ([contact]).

### Data sharing

The individual de-identified participant data, data dictionary, and statistical code generated during this study will not be publicly deposited in a repository. However, these materials are available upon reasonable request from the corresponding author, subject to compliance with applicable data protection regulations and approval by the Bioethics Committee of the Medical University of Gdańsk.

### Dissemination policy

The results of this trial will be submitted for publication in a peer-reviewed journal. Open access publication will be pursued where possible. Findings will also be presented at relevant national and international conferences. Upon completion of the study, participants who provided consent to be contacted will be informed of the key findings via the contact details collected at enrolment. No commercial dissemination is planned.
